## Abstract

**Background:**

The kidneys are a principal dose-limiting organ in radiotherapy for upper abdominal cancers. The current understanding of kidney radiation dose response is rudimentary. More precise dose-volume response models that allow direct correlation of delivered radiation dose with spatio-temporal changes in kidney function may improve radiotherapy treatment planning for upper-abdominal tumours.

Our current understanding of kidney dose response and tolerance is limited and this is hindering efforts to introduce advanced radiotherapy techniques for upper-abdominal cancers, such as intensity-modulated radiotherapy (IMRT). The aim of this study is to utilise radiotherapy and combined anatomical/functional imaging data to allow direct correlation of radiation dose with spatio-temporal changes in kidney function. The data can then be used to develop a more precise dose-volume response model which has the potential to optimise and individualise upper abdominal radiotherapy plans.

**Methods/design:**

The Radiotherapy of Abdomen with Precise Renal Assessment with SPECT/CT Imaging (RAPRASI) is an observational clinical research study with participating sites at Sir Charles Gairdner Hospital (SCGH) in Perth, Australia and the Peter MacCallum Cancer Centre (PMCC) in Melbourne, Australia. Eligible patients are those with upper gastrointestinal cancer, without metastatic disease, undergoing conformal radiotherapy that will involve incidental radiation to one or both kidneys. For each patient, total kidney function is being assessed before commencement of radiotherapy treatment and then at 4, 12, 26, 52 and 78 weeks after the first radiotherapy fraction, using two procedures: a Glomerular Filtration Rate (GFR) measurement using the ^51^Cr-ethylenediamine tetra-acetic acid (EDTA) clearance; and a regional kidney perfusion measurement assessing renal uptake of ^99m^Tc-dimercaptosuccinic acid (DMSA), imaged with a Single Photon Emission Computed Tomography / Computed Tomography (SPECT/CT) system. The CT component of the SPECT/CT provides the anatomical reference of the kidney’s position. The data is intended to reveal changes in regional kidney function over the study period after the radiotherapy. These SPECT/CT scans, co-registered with the radiotherapy treatment plan, will provide spatial correlation between the radiation dose and regional renal function as assessed by SPECT/CT. From this correlation, renal response patterns will likely be identified with the purpose of developing a predictive model.

**Trial registration:**

Australian New Zealand Clinical Trials Registry: ACTRN12609000322235

## Background

Radiotherapy has a significant role to play in the management of cancers of the upper abdomen, but high dose radiotherapy has been considerably limited by potential adverse normal tissue responses, in particular that of the kidneys. Because of their proximity to organs such as the pancreas, stomach and oesophagus, incidental radiation dose to the kidneys is frequently unavoidable when planning radiotherapy treatment. Our current understanding of kidney dose response and tolerance to radiation is rudimentary. This limits the delivery of a higher dose to the tumour and also the introduction and optimisation of new techniques to treat these upper gastrointestinal cancers, such as intensity modulated radiation therapy (IMRT).

Until recently, estimation of radiation-induced kidney damage was based on analysis of very basic radiotherapy data by Emami et al [1]. The Quantitative Analyses of Normal Tissue Effects in the Clinic (QUANTEC) review collated results of relevant studies that have been undertaken so far [2]. There have been previous key studies that have addressed the effects of partial kidney irradiation. In 1973, Thompson et al [3] reported the occurrence of clinical kidney toxicity several years after radiotherapy. Willet et al [4] found a dependence on the percentage of the volume being irradiated with a decrease in creatinine clearance. More recently, Kost et al [5] in 2002, used sequential scintigraphy to assess impairment of renal function and correlated it with the radiation dose distribution. Jansen et al [6] observed a progressive decrease in renal function in gastric cancer patients after postoperative radiotherapy. Studies in pigs [7,8] have shown that the response is dependent on whether one or both kidneys are irradiated and that the functional response depends on the compensatory response of the non-irradiated kidney.

A review of the preceding studies and the QUANTEC report [2] has highlighted several key points which have influenced the design of the RAPRASI study protocol:

– Kidneys have a late response to radiation (between 3 and 18 months).

– The functional response is dependent on the percentage of the kidney volume being irradiated and the dual nature of this organ influences their response.

– There is limited quantitative data to support dose-volume models for the kidney. Studies are required with collection of data that would allow correlating regional kidney function over time with the radiation dose distribution received in the radiotherapy treatment.

– The glomerular filtration rate (GFR) should be used to assess the toxicity of the kidney, as recommended by the National Kidney Foundation [9]. Early changes in renal perfusion and GFR correlate with an increased risk of late toxicity [2] and chronic injury is unlikely if changes in GFR and perfusion are not detected by 24 months after irradiation [10,11].

– Significant technological advances in imaging offer the possibility to study late responding normal tissues using quantitative functional imaging instead of a conventional histological analysis [12].

GFR can be estimated using serum creatinine levels and estimating equations but in order to achieve a higher degree of accuracy, a ^51^Cr-ethylenediamine tetra-acetic acid (EDTA) clearance measurement should be used. On the other hand, scintigraphy with Single Photon Emission Computed Tomography (SPECT) can provide greater detail regarding the relative distribution of kidney function; kidney perfusion as indicated by uptake of ^99m^Tc-dimercaptosuccinic acid (DMSA), imaged with scintigraphy, has been shown to correlate with relative regional function [13,14]. Sequential GFR measurements using the ^51^Cr-EDTA clearance and SPECT imaging undertaken before, during and after radiotherapy, allows observation of regional functional changes in the kidney over time and these changes can be correlated with the radiation dose delivered during radiotherapy.

In order to quantify the relationship between radiation dose delivery and kidney response, methods are required that will allow the registration of the estimated three-dimensional (3D) radiotherapy dose distribution to the regional changes in kidney function, indicated by changes in DMSA uptake [15]. In a SPECT/CT system [16], both Computed Tomography (CT) and SPECT imaging is undertaken on the one device with the patient in a single position. This minimises any influence of patient motion or physiological changes between the two imaging studies, allows simple fusion of the two resulting image sets and also gives the anatomical reference to relate kidney position. The CT component also facilitates attenuation correction of the SPECT data which enables accurate quantification of regional radiotracer uptake. Sequential SPECT/CT studies can be spatially registered to planned radiotherapy dose distributions, via registration of the accompanying CT component to the CT images obtained for radiotherapy treatment simulation and planning.

Results from a pilot study at SGH are shown on Figure 1.

**Figure 1 F1:**
[figure not shown]
**A preliminary qualitative example.** Sample patient data from a pilot study at SCGH. The images are coronal slices, the grey shapes are the outlines of the kidneys. **a)** Planned radiotherapy dose distribution (yellow 45 Gy to black 0 Gy) and kidney volumes. **b)** Baseline (pre-treatment) SPECT intensity distribution (red - high activity, blue – low activity). **c)** 12-week post treatment SPECT showing reduced perfusion in the high-dose region.

### Study hypotheses

An assessment of changes in total kidney function (using GFR measurement), regional kidney functional change (using SPECT imaging) and their correlation with radiotherapy dose delivery is within the means of currently available imaging, therapy and computational technology. The hypotheses being tested in RAPRASI are:

– Temporal variations in SPECT images of the kidneys correlate with patterns of radiation dose delivery in the kidneys.

– Models of kidney response developed from SPECT-response studies can be used to predict changes in kidney function as a result of radiation therapy.

The principal aim of RAPRASI is to obtain a better understating of kidney response when a patient is receiving radiotherapy for an upper-abdominal cancer. This will involve monitoring the spatial and temporal changes in kidney function for correlation with delivered three-dimensional radiation dose distribution. A more precise dose-volume response model for kidney will not only improve our current understanding but may permit further optimisation of radiation therapy techniques for upper-abdominal tumours.

## Methods/design

### Study design and schedule

RAPRASI is a clinical research study for participants with upper gastrointestinal malignancies (without metastatic disease) and who have controlled and stable kidney function. Radiotherapy treatment technique is according to local departmental protocols. Participants are being recruited as they present to the Department of Radiation Oncology, Sir Charles Gairdner Hospital (SCGH) in Perth, Australia, and to the Department of Radiation Oncology, Peter MacCallum Cancer Centre (PMCC) in Melbourne, Australia. The protocol has been approved by both institutional ethics committees. All patients are required to give written informed consent.

In addition to a baseline visit, timed to coincide with participants having a CT scan for the purpose of radiotherapy simulation, participants will have follow-up visits at 4, 12, 26, 52 and 78 weeks subsequent to the first radiotherapy treatment fraction. On each occasion they will undergo: a sequential ^99m^Tc-DMSA SPECT/CT (simultaneous SPECT and CT images), a GFR measurement (^51^Cr-EDTA clearance), a full blood count and assessment of blood urea and electrolytes.

The timing of SPECT/CT scans is intended to reveal i) acute and sub acute changes in total kidney function (GFR measurement) before and following radiotherapy, ii) information on kidney positioning before and following radiotherapy, and iii) the time-dependence of changes in regional kidney function and position (SPECT/CT scans) before and following treatment.

### Inclusion criteria

– Males or females older than 18 years of age.

– Histologically/cytologically proven upper GI adenocarcinoma.

– Signed written informed consent provided to participate in the study.

– Radical radiotherapy (dose > 40 Gy in 4 weeks) being prescribed to an upper abdominal site that will involve incidental radiation of one or both kidneys.

– Loco regional staging of primary disease will have been undertaken with dual phase (arterial and portal) spiral CT.

– Serum creatinine ≤150 *μmol/L.*

– Performance status is ECOG grade 0, 1 or 2 [17].

### Exclusion criteria

– Major co-morbid illnesses that, in the opinion of the investigator, would prevent the patient undergoing planned SPECT/CT scans during the first year following treatment.

– Evidence of metastatic disease.

– Significant loss of bodyweight (>15% weight loss since diagnosis).

– Inadequate bone marrow function to undergo planned therapy.

– Previous drug-induced nephrotoxicity and/or planned treatments that are likely to cause drug-induced nephrotoxicity.

– Previous abdominal radiotherapy.

– Pregnancy or lactation.

### Data collection and quality assurance

This study will be conducted according to the Human Research Ethics Committee (HREC)-approved study protocol and the ‘Note for Guidance on Good Clinical Practice (CPMP/ICH/135/95) annotated with TGA comments’ (Therapeutic Goods Administration DSEB July [18]. The study will be performed in accordance with the NHMRC ‘National Statement on Ethical Conduct in Human Research’ (© Commonwealth of Australia 2007) and the ethical principles within the ‘Declaration of Helsinki’ (Revised 1996) [19].

Sir Charles Gairdner Hospital will act as the sponsor of this study at both the Peter MacCallum Cancer Centre and Sir Charles Gairdner Hospital in Perth, Western Australia. Standard medical care (prophylactic, diagnostic and therapeutic procedures) remains the responsibility of the patient’s treating physician.

The investigator is responsible for ensuring that no participant undergoes any study related examination or investigations prior to obtaining written informed consent. The investigator will explain the aims, methods, possible benefits and potential hazards before the participant gives consent. The participant will be given sufficient time to read the documentation, understand the project and have any questions addressed prior to signing the consent form. The participants will be advised that they have the right to withdraw their consent to participate at any time without any consequences.

Participant confidentiality will be protected at all times. In any resulting publication or presentation, no patients will be identified.

Records will be retained for 15 years post study completion in a locked facility, in accordance with TGA requirements. Access to participant study records will be limited to treating clinician, chief investigator, his/her nominated co-investigators and the local study co-ordinators.

Collation of data will yield the following for each participant:

– Local kidney function/response to therapy: regional change in SPECT signal intensity:

•from baseline to 4 weeks post start of radiotherapy

•from baseline to 12 weeks post start of radiotherapy

•from baseline to 26 weeks post start of radiotherapy

•from baseline to 52 weeks post start of radiotherapy

•from baseline to 78 weeks post start of radiotherapy

– Planned 3D Regional radiation dose distributions intended to be experienced during radiation treatment.

– Kidney function measure: GFR at baseline, 4, 12, 26, 52 and 78 weeks.

– Indication of existing and acquired co-morbidities.

– Information on adjuvant treatments.

GFR measurements using the ^51^Cr-EDTA clearance and Digital Imaging and Communication in Medicine (DICOM) formatted SPECT/CT images will be obtained on Siemens Symbia T6 SPECT/CT scanners located in the Department of Nuclear Medicine at SCGH and the Centre for Molecular Imaging at the PMCC. These images involve pre-injection of approximately 185 MBq of ^99m^Tc-DMSA (Radpharm DMS 1987/1), providing 128x128 pixel attenuation-corrected images reconstructed at approximately 5 mm pixel resolution. SPECT images are automatically registered to CT taken on the same device (6 slice helical CT scanner), with image settings sufficient for organ definition and bone matching with minimal radiation dose (typically 130 kV, 80-100 mA, 5 mm slice thickness). SPECT pixel intensity values will be normalised according to calibration images obtained on the scanner during monthly quality-assurance checks. SPECT data will be reconstructed using an ordered subset expectation maximization (OSEM) algorithm incorporating CT attenuation data.

Treatment plan data (images, structures, beam definitions, dose-volume data, and 3D dose distribution) will be exported in DICOM-RT format from the Treatment Planning System. (CMS XiO at SCGH, Varian Eclipse at PeterMac). Digitally reconstructed radiographs (DRRs) will be generated indicating local bony anatomy (upper pelvis, spine, ribs) and the location of kidneys from the planning CT. Variation in kidney position relative to local bony anatomy is of the order of SPECT image resolution [20,21]. Patient localisation will initially be to external marks, with on-line positioning then corrected according to localisation images spatially matched to the DRRs. Localisation images will be obtained either with the Brainlab Exactrac system (6D patient positioning) [22] or the Varian On-Board Imaging system (3D positioning) [23]. Applied patient shifts will be recorded together with localisation images. Where possible, kidney position will be identified on the localisation images for comparison with planned kidney outlines, as per standard departmental practice.

It is anticipated that all participant data will be utilized in the final analysis provided that each participant completes at least the baseline (pre-radiotherapy) and first SPECT/CT scan at 4 weeks post start of radiotherapy. If a participant commences radiotherapy (i.e. completes the baseline SPECT/CT scan) but withdraws consent mid-treatment or is unable to complete any further SPECT/CT scans, then the data for that participant will be excluded from the final analysis.

Data relating to co-morbidities and concurrent treatments, including adjuvant chemotherapy, known to influence kidney toxicity [2], will be extracted from participant notes.

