### Statistical considerations

A target of 30 complete participant datasets has been set based on an assessment of anticipated patient numbers, recruitment and attrition rates, together with a power calculation of the number of datasets required to indicate a statistically significant variation in SPECT image intensity. A clinically significant difference would be a reduction of 20% from baseline to a follow-up imaging study [5]. In order to detect a conservative estimate of a 10% reduction, where the measurement error is 20% we would require a sample size of 33 (using a paired t-test with alpha = 0.05 and power = 80%; detecting 10.5% with 30 patients which is sufficient). With an anticipated 20% non-completion/attrition rate, allowance will be made for up to 40 recruited patients. Given the intensive data analysis required per patient dataset in this study, 30 datasets represents an upper-limit in terms of manageability.

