iv. An export of co registered dose and SPECT information will be made for regions defined by whole kidneys, separately-identified medulla and cortex, baseline-image functional regions, and at varying spatial resolutions. Renal response patterns obtained from variations in SPECT and GFR shall be fitted to normal-tissue complication probability (NTCP) and equivalent uniform-dose (EUD) models, as previously undertaken by CI’s using estimated parameters [27,28]. Response indicators can be related to dose volume histogram (DVH) and dose-function histogram (DFH) data by maximum likelihood fitting to the parametric NTCP/EUD models. For this purpose, the freely available DREES code [29], developed in Matlab, will be utilised. Separate analyses will be undertaken using acute changes in SPECT signal (< 12 week images) as well as the long-term changes indicated by images taken at 52 or 78 weeks post-radiotherapy.

Examination of the predictive nature of response models will be made by establishing parameters based on the first 20 patient data sets, and utilising the models to predict SPECT signal changes on the subsequent 10 patients. In order to minimise parameter uncertainties however, final parameter values will be based on data for all patients.

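### The final analysis is conditional on the 4-week scan, which conflicts with the next sentence; separately, the item iv time windows leave week 26 (and, read strictly, week 12) unassigned

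*Protocol article*

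**What the plan says.** **Who is analysed.** Data collection and quality assurance expects to use all participant data "provided that each participant completes at least the baseline (pre-radiotherapy) and first SPECT/CT scan at 4 weeks post start of radiotherapy". The sentence after it names two grounds for leaving out a participant who has started radiotherapy. One is consent withdrawn during treatment. The other covers someone who "is unable to complete any further SPECT/CT scans, then the data for that participant will be excluded from the final analysis".

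**When scans are taken.** Under Study design and schedule, "participants will have follow-up visits at 4, 12, 26, 52 and 78 weeks subsequent to the first radiotherapy treatment fraction". Background gives the expected timing of the effect: "Kidneys have a late response to radiation (between 3 and 18 months".

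**How scans are grouped in item iv.** For the NTCP and EUD fits, Data analysis plans separate analyses "using acute changes in SPECT signal (< 12 week images) as well as the long-term changes". It takes the long-term changes from images at 52 or 78 weeks, counted there from radiotherapy without saying from its start. Item i of the same section has no such grouping. It compares time-points within each participant and fits a repeated-measures mixed model with a random subject effect over all participants.

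**The concern.** The first sentence sets a positive condition (baseline and week 4). The second sets an exclusion (no scan after baseline, or mid-treatment withdrawal). They should describe the same set of people, and they do not. The case left open is the participant who misses one early visit and then attends the later ones.

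That participant carries much of the information the study wants, because the later scans lie in the period when the protocol expects damage to show. Under the literal first rule, someone with baseline and week 4 alone is kept, while someone with baseline and four later scans is dropped. If patients miss week 4 because they tolerate treatment badly, the rule would also select on something related to outcome. The documents neither show nor rule that out. While the rule is unsettled, the analysis set could be chosen after the data are seen.

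The item iv windows raise a smaller, separate question: which fit, if any, receives the scans between the acute and the long-term sets.

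**Working it through.** **1. The two rules side by side.**

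| Scans completed | First sentence | Second sentence |
|---|---|---|
| Baseline only | not analysed | excluded |
| Baseline and week 4 | analysed | not excluded |
| Baseline, 12, 26, 52, 78 (week 4 missed) | not analysed | not excluded |

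Only the last row is in conflict.

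**2. Where each visit falls.** At 52/12 = 4.33 weeks per month, 3 months is 13 weeks and 18 months is 78 weeks. Week 4 is 4/4.33 = 0.9 months and week 12 is 2.8 months. Weeks 26, 52 and 78 are 6, 12 and 18 months. The inclusion criterion describes a dose above 40 Gy in 4 weeks, so the required scan falls at about the end of such a course and before the stated response period. Week 12 is at the edge of that period and the other three visits are inside it.

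**3. The plan's own sample size.** Inputs from Statistical considerations: 10% reduction, 20% measurement error, paired t-test, alpha 0.05, power 80%.

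- Normal approximation: n = ((1.960 + 0.842) × 20/10)² = 31.4, so 32.
- Exact two-sided paired t-test (noncentral t, n − 1 degrees of freedom, noncentrality (10/20)√n): n = 34, with power 79.5% at n = 33.
- Detectable reduction at n = 30 with 80% power: 10.6% by exact t, against the stated 10.5%.

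The stated 33 lies between the two methods. The sample-size arithmetic is not at fault, and it uses 20% as the SD of the paired difference.

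**4. What the literal rule could cost.** From 40 recruits and 20% attrition, 40 × 0.80 = 32 remain. The documents give no rate for missing only week 4, so a share m is assumed. The table assumes that all 32 have the later scan being compared, and uses n = 32 × (1 − m), rounded down, with the exact t-test of step 3.

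| m (assumed) | n | Power for a 10% reduction | Detectable at 80% power |
|---|---|---|---|
| 0% | 32 | 78% | 10.2% |
| 5% | 30 | 75% | 10.6% |
| 10% | 28 | 72% | 11.0% |
| 15% | 27 | 71% | 11.2% |
| 20% | 25 | 67% | 11.7% |

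This applies to comparisons of baseline with later visits. For the week-4 comparison itself, these participants have nothing to contribute under either rule.

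**5. The item iv windows against the schedule.**

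| Visit | Separate fit in item iv | Available to item i |
|---|---|---|
| Week 4 | acute | yes |
| Week 12 | none if under 12 is strict; acute if loosely meant | yes |
| Week 26 | none on either reading | yes |
| Weeks 52 and 78 | long-term | yes |

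**The case against.** **The explicit exclusion may be the operative rule.** The first sentence opens with an intention to use everyone's data, and the only sentence that excludes anyone does not reach the participant in question. This is fair. It means one cannot say that such patients will be dropped, only that one of two conflicting sentences drops them.

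**Week 4 has a purpose.** Study design and schedule names acute and subacute changes as a target, and Background says that early perfusion and GFR changes correlate with late toxicity. This justifies taking the scan and running an early analysis. It does not justify making that scan a condition for using the later ones, since a repeated-measures mixed model accepts a missing visit.

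**Stronger readings that the documents do not support:**

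- *The 12- and 26-week images are thrown away.* The windows govern only the separate fits in item iv. The baseline-to-12-week and baseline-to-26-week changes are listed for collation, and item i uses time-points without a window.
- *The trial leaves out the visit where the pilot saw the effect.* Figure 1 shows a "12-week post treatment SPECT showing reduced perfusion in the high-dose region", labelled as a preliminary qualitative example. Counted from the end of a course of about 4 weeks, that is roughly week 16 from the first fraction, not the week-12 visit.
- *There is a third definition of the analysis set.* "A target of 30 complete participant datasets has been set" states a recruitment target, not a rule for who is analysed.
- *Averaging weeks 4 and 12 would give a known gain in precision.* Such a figure needs 20% to be the error of each scan, which conflicts with step 3. It also needs the same response at both visits.
- *The choice between 52 and 78 weeks invites selective reporting.* The wording may mean whichever late image exists, and a condensed article can leave that to the full protocol.

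**Conclusion.** The point stands in two parts of unequal weight.

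First, the two sentences on the analysis set contradict each other for a participant who misses week 4 and returns. The literal first rule would remove scans from the period the study is about. The size cannot be computed from the documents. Under the assumed 5–20% range, power for a 10% reduction is 67–75% against 78%. The detectable reduction is at most 11.7%, well below the 20% that the protocol calls clinically significant. The effect on power is therefore modest. The stronger reasons to change the rule are possible selection and an unsettled analysis set.

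Second, and within item iv only, week 26 belongs to neither separate NTCP/EUD fit, and week 12 belongs to neither if the limit is strict. Item iv also words its long-term times differently from the schedule, which counts from the first fraction. These are points to settle in the wording and do not amount to data loss across the study.

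**What to change.** - **Analysis set.** Replace the proviso with: baseline and at least one follow-up SPECT/CT scan. Reword the next sentence so that it excludes exactly those who do not meet this condition, and say how scans obtained before a withdrawal are handled.
- **Item iv.** Assign every visit to a window. For example: weeks 4 and 12 as early, with time distinguished in the fit and not averaged; week 26 as intermediate; weeks 52 and 78 as late, using both when available.
- **Clock.** Count all times from the first fraction, as the visit schedule does.

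**Cost.** A few sentences, no extra scans, a few more datasets to process and one more model fit. The protocol calls 30 datasets the limit of what is manageable. With the stated attrition, the wider rule would bring at most 32, or 2 more.
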